## ***Procedures / Study Schedule***

The study will be conducted by Good Clinical Practice (GCP) certified researchers. The reference product and test products will be administered to participants in a randomised, repeated measures design. On the day prior to a test, participants will be asked to restrict their intake of alcohol and caffeine-containing drinks and to restrict their participation in intense physical activity (for example, long periods at the gym, excessive swimming, running, aerobics). Participants will also be told not to eat or drink after 10.00 pm the night before a test, although water will be allowed in moderation. Participants will be studied in the morning after an overnight fast. Participants will consume the products at a comfortable pace, within 5 minutes. The reference product and test products will be served with 50g maltodextrin dissolved in 250 ml water. Participants will remain sedentary during each test session and will not consume any additional food or fluid. Participants will be instructed to record stool consistency for the first bowel movement after their visit and the frequency and intensity of gastro intestinal symptoms for 0-24 hours after the study product consumption.

All anthropometric measures will be taken, using standard methods, in the morning, after an overnight fast.

- Height and weight
- BMI will be calculated using the standard formula:  $\text{weight (kg)} / \text{height (m}^2\text{)}$
- Waist and hip circumference

The glycaemic response method used is adapted from that described by Brouns *et al.* [22] and is carried out in accordance with the ISO 26642:2010 standards. Blood measurements will be taken at -5 min and 0 min before consumption of the reference product/test products and the baseline value taken as a mean of these two values. Further blood measurements will be taken at 15, 30, 45, 60, 90 and 120 minutes after starting to eat. Blood glucose will be measured using the HemoCue Glucose 201+ analyser (HemoCue® Ltd). The same time points will be used for determining insulin levels. At each test time point, 300 µL of capillary blood (from finger pricks) will be obtained. Finger pricks will be made using the Unistik 3 single-use lancing device (Owen Mumford, Woodstock, UK) and blood will be collected into chilled Microvette® capillary blood collection tubes treated with di Potassium EDTA (CB 300 K2E; Sarstedt Ltd., Leicester, UK). The Microvette® tubes will then be centrifuged and 200 µL of the supernatant plasma obtained. Insulin concentrations in the plasma samples will be determined by electrochemiluminescence immunoassay using an automated analyzer (Cobas® E411; Roche diagnostics, Burgess Hill, UK). The Cobas® system is a reliable method of plasma insulin determination. The unit of measurement is µU/ml. Sufficient blood is taken to enable 2 sets of analysis to be performed at every time point thus greatly reducing the likelihood of missing data.

## ***Statistical Analysis***

This is the first rigorous study of IM and should therefore be considered as a pilot study from a statistical perspective. We will calculate the incremental area under the curve for all 4 study products and compare using repeated measures ANOVA to determine whether there is a statistically significant difference in plasma glucose levels and in secondary outcome measure over the 120 minute period. All models will control for the possible confounding effects of sex and BMI. The presence/absence of gastrointestinal symptoms in the 24 hours following the study visit will be assessed using logistic regression models. We anticipate a low likelihood of missing data (as sufficient blood is taken for a second analysis to be performed if the first analysis fails) and our glucose values will be measured in real time. We anticipate monophasic or biphasic glucose and insulin curve responses and will use a 2nd order interpolation method for missing data, provided that no other data is missing from the two neighbouring time points at either side of a missing data set and that the baseline and end data values are obtained. If the baseline or end points are missing or more than one data point within five neighbouring time points, this data set will be deemed unsuitable and not be included in the analysis.

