## **Methods / Design**

### ***Objectives***

The primary objective is to determine the effect of three doses of mulberry-extract (IminoNorm®) versus placebo on blood glucose and insulin responses when co-administered with 50g maltodextrin in normoglycaemic healthy adults. We also aim to determine the gastrointestinal tolerability of the mulberry extract using both normal (250mg IminoNorm® capsule containing 12.5mg 1-deoxynojirimycin), half (125mg IminoNorm® containing 6.75mg DNJ), and double (500mg IminoNorm® containing 25mg DNJ) the normal dose. The ME (IminoNorm®) is provided by Phynova Group Ltd, UK.

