### ***Hypothesis***

Our primary hypothesis is that an appropriate dose of mulberry extract co-administered with oral maltodextrin will reduce the incremental area under the curve for plasma glucose concentration over 120 minutes in normoglycaemic adults in a dose-dependent manner when compared to co-administration with placebo. Our secondary hypothesis is that mulberry extract co-administered with oral maltodextrin will not disproportionately increase the incremental area under the curve for plasma insulin concentration over 120 minutes in normoglycaemic adults compared to co-administration with placebo.

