### **Study Design**

A double-blind, randomised, repeat measure, crossover design trial will be used to study the glycaemic response (GR) and insulinaemic response (IR) to three products: one reference product and three test products. Participants will act as their own controls, i.e. each participant will test all four products. The trial will be conducted by the Functional Food Centre at Oxford Brookes University. Ethical approval for the study has been obtained from the University Research Ethics Committee (UREC) of Oxford Brookes University, Faculty of Health and Life Sciences, [name]. Participants will be given full details of the study protocol and the opportunity to ask questions. All participants will give written informed consent prior to participation.

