### ***Sample Size***

A recent study in India (which is yet to be published) in 12 healthy individuals age 18-25 using 250mg ME dose showed a reduction in the glycaemic index of maltodextrin by 58% when compared to placebo. A sample size of 30 would allow over 90% power to detect a difference of a similar size. Being more conservative and allowing for a smaller difference to be detected in the lower concentration doses, 30 participants would still allow at least 80% power to detect a difference of 25% in the incremental Area Under the Curve (iAUC). In order to account for a potential loss to follow up, and the possibility that our sample size may be inaccurate as it is based on a small pilot sample we will therefore recruit 40 participants.

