### ***Outcomes***

Primary outcome:

iAUC for plasma glucose concentration over 120 minutes.

Secondary outcomes:

- iAUC for plasma insulin concentration over 120 minutes.
- Gastrointestinal tolerability – abdominal bloating may be experienced due to reduced carbohydrate absorption. Gastrointestinal symptoms will be measured via questionnaire for 24 hours following each study visit. Subjects will use a 5-point scale to rate stool consistency for each bowel movement for 0-24 h after the study product consumption. The five-point scale includes: 1=watery, 2=loose/mushy, 3=soft, 4=formed, 5=hard. Frequency and intensity will be set to a 10-centimeter (cm) line scale (0 representing "Absent" for frequency and "Usual" for intensity; 10 representing "More than usual" for frequency and "Severe" for intensity).

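### The primary hypothesis is a dose-dependent reduction versus placebo, but the only test the protocol fixes asks whether four products differ at all

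*Protocol*

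**What the plan says.** - **Hypothesis.** The extract "will reduce the incremental area under the curve for plasma glucose concentration over 120 minutes in normoglycaemic adults in a dose-dependent manner"; the stated comparator is placebo. This is a directional claim, against a named comparator, with an ordering over doses.
- **Objectives.** "The primary objective is to determine the effect of three doses of mulberry-extract (IminoNorm®) versus placebo on blood glucose and insulin responses".
- **Outcomes.** The primary outcome is "iAUC for plasma glucose concentration over 120 minutes".
- **Study Design.** The comparison is within person: "each participant will test all four products".
- **Statistical Analysis.** After computing iAUC for all four products, the plan is to "compare using repeated measures ANOVA to determine whether there is a statistically significant difference in plasma glucose levels". The section names no contrast with placebo and no trend. It also calls the trial a pilot from a statistical perspective.
- **Sample Size.** Over 90% power with 30 participants is claimed for a difference like the 58% fall in glycaemic index seen at 250 mg in an external study of 12 people. For the lower doses, "30 participants would still allow at least 80% power to detect a difference of 25% in the incremental Area Under the Curve (iAUC". Forty are to be recruited. No SD, alpha, sidedness or comparison is attached to either figure.

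**The concern.** The hypothesis and the named test ask different questions. A repeated measures ANOVA over four products gives an overall F test of equality of the four means. It can be significant for any pattern of means, including one where only the lowest dose does anything or where an active product raises iAUC. A significant result therefore cannot by itself support the claim in the Hypothesis section.

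The Discussion raises the stakes. The trial is meant to confirm a standard dose and to supply an effect size that may be used to plan a larger trial. Both uses need estimates for each dose against placebo, in order of dose. If those comparisons are added informally after a significant F, their joint error is not held at 5%.

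The Sample Size section speaks of individual doses, while the analysis section names no dose-level test. A reader cannot tell which test the power belongs to.

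**Working it through.** **Inputs from the protocol.** n = 30 for power and 40 recruited; a 25% difference at 80% power or more; a 58% difference at over 90%; four products per person; doses 0, 125, 250 and 500 mg.

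**Assumptions (not in the protocol).** Two-sided alpha 0.05; a paired t test on iAUC as a percentage of the placebo mean; exactly 80% power; equal variances and correlations across products.

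**1. Plan's own figure.** The 80% cannot be reproduced without an SD, so the SD is back-solved. For a paired t test with 29 df, 80% power needs a standardised difference of 0.529:

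- SD of the paired difference = 25 / 0.529 = 47.2% of the placebo mean (normal approximation 48.9%; one-sided alpha 0.05 would give 53.8%).
- Within-person variance = 47.2² / 2 ≈ 1,116, so within-person SD ≈ 33.4%.
- At this SD, power for 58% exceeds 99.9%, so the two stated power figures are compatible.

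**2. Overall F when only 125 mg works (0/25/0/0).** Noncentrality λ = n Σ(mᵢ − m̄)² / σ²:

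- m̄ = 6.25; Σ = 18.75² + 3 × 6.25² = 468.75
- λ = 30 × 468.75 / 1,116 = 12.6
- Power with 3 and 87 df = **84%**

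The test succeeds in about five trials out of six although dose-dependence is false.

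**3. A true gradient (0/8.3/16.7/25).**

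- Overall F: Σ = 2 × 12.5² + 2 × 4.17² = 347.2; λ = 30 × 347.2 / 1,116 = 9.3; power **71%** (84% at n = 40).
- Linear contrast in mg, with coefficients −218.75, −93.75, 31.25, 281.25: Σcm = 6,771; SE = √(1,116 × 136,719 / 30) ≈ 2,255; ratio 3.00; power **84%** (86% with equally spaced scores).

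**4. Family-wise error of three comparisons with placebo** (simulation, n = 30).

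| Situation | Chance of at least one false claim |
|---|---|
| All doses inert, no gate, each at 5% | about 12.7% |
| One dose active, tests only after a significant F | about 9% |

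When every dose is inert, the F gate holds the error at or below 5%. Once one dose works, the gate is nearly always open and the other two doses are tested unprotected.

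**5. Per-dose power for 25%, if the stated 80% is one unadjusted comparison.**

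| Procedure | n = 30 | 40 completers |
|---|---|---|
| Unadjusted | 80% | 90% |
| Bonferroni (0.05/3) | 64% | 79.7% |
| Dunnett (87 df at n = 30) | 69% | not computed |

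Bonferroni reaches 80% at 41 completers.

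**6. Can a trend contrast simply replace the F?** Not without cost. With a plateau (25% at all three doses, n = 30), the mg-scaled contrast has 67% power against 84% for the F. When only 500 mg works, it rejects 87% of the time. It tests dose-dependence better than the F does, but it is a poor gate for claims about individual doses.

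**The case against.** **Contrasts and multiplicity rules usually sit in a SAP, and none is shown.** This stands as far as it goes. The analysis section does not forbid follow-up contrasts, so their absence is not the point. The point is that the protocol itself states one question as its hypothesis and another as its test.

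**The trial is a declared pilot, with recruitment finished.** This stands and lowers the severity. Requoting power cannot change the sample. It does not remove the mismatch, because the Discussion still relies on dose-level conclusions.

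**A reader might infer that the stated 80% is valid only for one unadjusted dose comparison.** The documents do not support that. The Sample Size section does not name the comparison, and its figure is a lower bound. At the back-solved SD the overall F itself reaches 84% when one dose or all three differ by 25%. Holm keeps 80% for a 25% low dose if the other two reach 58%, and Bonferroni gives 79.7% with 40 completers.

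**A reader might also infer that the ANOVA inflates type I error through unequal variances.** Simulation does give 10–14% for an inert 125 mg dose, against about 5% with that contrast's own variance. This needs SD proportional to the mean, pooled-error pairwise tests, and an inert low dose beside reductions of 25–58% at the higher ones. The protocol states none of these. Nor does it forecast such reductions: the 58% is an external glycaemic-index result and the 25% a detectable difference. The figures are only a reason to prefer contrast-specific variances.

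**Conclusion.** The mismatch is real and does not depend on any assumed SD: an overall F test has no direction, names no dose and ignores dose order, while the primary hypothesis specifies all three.

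Its size is conditional on the 47% paired-difference SD, two-sided 5% tests and equal variances. On that basis, the named test succeeds about 84% of the time in a pattern that contradicts the hypothesis. It gives up about 13 points of power on the gradient shown (71% against 84%). Used as the only gate, it leaves a family-wise error of about 9% when one dose works. A smaller true SD would raise every power figure.

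The power statement is unclear rather than shown to be wrong. This should be corrected before unblinding; given the pilot status it is not a critical defect.

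**What to change.** Before the randomisation code is broken:

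1. In Statistical Analysis, base the primary claim on pre-specified dose-versus-placebo contrasts from the within-subject model, with family-wise error controlled. One option is a fixed testing sequence of 500, 250, then 125 mg, each at two-sided 5%, stopping at the first non-significant step. Holm or Dunnett are alternatives. Give each contrast its own paired-difference variance and a 95% CI.
2. Report a linear dose-trend contrast as the test of dose-dependence, without making it a gate for the dose comparisons.
3. In Sample Size, state which comparison, alpha, sidedness and SD the 80% refers to, and quote power under the chosen procedure.

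**Cost.** Wording only; no participants, visits or samples. In a fixed sequence a lower dose cannot be claimed if a higher one fails. Holm or Dunnett avoids that for some loss of power. With most participants already through all four visits, the contrasts are credible only if they are recorded and dated before unblinding.

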### ***Study Period***

In each participant, the reference product and test products will be tested in random order on (four) separate days, with at least a two-day gap between measurements to minimise carry over effects. The study schedule is summarised in Table 2.

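### Sex and BMI cannot confound a within-person product comparison: drop that rationale, add period to the model, and keep BMI only if it is centred

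*Protocol*

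**What the plan says.** The Study Design section makes every comparison within-person: "Participants will act as their own controls, i.e. each participant will test all four products". Under Study Period, "the reference product and test products will be tested in random order on (four) separate days"; the visits are to be two or more days apart, so that one product does not affect the next. The primary outcome is "iAUC for plasma glucose concentration over 120 minutes". Each visit has its own fasting reference, from samples at -5 and 0 minutes, with "the baseline value taken as a mean of these two values" (Procedures / Study Schedule).

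The Statistical Analysis section will calculate the incremental area for the four products and "compare using repeated measures ANOVA to determine whether there is a statistically significant difference in plasma glucose levels", with the same comparison for the secondary measure. It then adds: "All models will control for the possible confounding effects of sex and BMI". That covers the gastrointestinal models as well: "The presence/absence of gastrointestinal symptoms in the 24 hours following the study visit will be assessed using logistic regression models".

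The section names no period or sequence term. It does not say whether BMI is centred or crossed with product. Table 2 schedules BMI at each of the four visits, and the text does not say which value is used.

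**The concern.** A confounder must differ between the conditions compared. In a four-product crossover with visits days apart, sex does not differ and BMI hardly does. The stated reason for the adjustment therefore does not apply to this design.

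The choice could still matter, because common repeated-measures ANCOVA routines cross a person-level covariate with the within-person factor. The product main effect is then the effect at covariate value zero. For sex and BMI read literally as covariates in a repeated measures ANOVA, that is one plausible implementation, and it would remove most of the power that the Sample Size section counts on.

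Meanwhile the factor that does vary within a person by design, the visit at which a product is taken, is not in the model.

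**Working it through.** **The plan's own power figure.** The Sample Size section claims at least 80% power for a 25% difference in iAUC with 30 participants, and over 90% for 58%. It gives no SD and no alpha, so neither figure can be reproduced. Solving a paired t-test backwards (two-sided 0.05, assumed) for 80% at 25% and n = 30 gives an SD of the within-person difference of 47.2% of the placebo mean (40.2% if alpha were 0.05/3). At 47.2%, power for 58% exceeds 99.9%, so the two claims agree with each other. The within-person SD is 47.2/√2 = 33.4%, used below.

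**Sex and BMI as main effects.** For participant i, the difference between a dose and placebo is D_i = Y_i(dose) − Y_i(placebo). A term β × BMI_i appears in both and cancels; sex does the same. In one simulated complete data set, a mixed model gave product estimates of −30.16, −20.51 and −26.77 with SE 7.39, identical with and without sex and BMI.

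**Raw BMI crossed with product.** Now D_i = δ + γ × BMI_i + error, and the product test asks whether δ, the effect at BMI = 0, is zero. Table 1 confines BMI to about 20 to 30. Relative to no covariate, the variance of the contrast is multiplied by

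1 + (mean²/SD²) × n/(n − 1).

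With mean 25, SD 2.9 and n = 30 (BMI distribution assumed):

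- 25²/2.9² = 74.3; 74.3 × 30/29 = 76.9; adding 1 gives 77.9. The SE is multiplied by √77.9 = 8.8.
- The SE without BMI is 47.2/√30 = 8.6 points. With raw BMI it is 8.6 × 8.8 = 76 points, so a 25-point effect is about 0.33 SE.
- Power for one contrast is 6.2%, against 80%.
- Over BMI mean 24 to 25, SD 2 to 3.5 and n = 30 or 40, the SE is multiplied by 7.0 to 12.8. Power for 25% is 5.6 to 7.5%, against 80% (n = 30) or 90% (n = 40). For 58% it is 8 to 19%.

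Omnibus product test, 4,000 simulated trials, n = 30, BMI uniform on 20 to 30, 25% reduction at every dose:

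| Model | Power |
|---|---|
| No covariate | 83.9% |
| BMI centred | 84.2% |
| BMI raw, crossed with product | 5.8% |

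Under the null with no BMI-by-product interaction, all three reject about 5% of the time. With an interaction of 2% per BMI unit and no effect at the mean BMI, the raw-BMI test rejects 8.8%.

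**Period.** Power for one dose against placebo, without and then with a period term, from 1,500 trials per row. Drift is the assumed total linear change over four visits, as a percentage of the placebo mean.

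| Drift | Unrestricted random order, n = 30 | Williams sequences, n = 32 |
|---|---|---|
| 0% | 80.6 → 77.8 | 82.9 → 83.1 |
| 10% | 81.7 → 81.3 | 83.0 → 83.5 |
| 20% | 78.1 → 80.2 | 81.7 → 83.7 |
| 30% | 73.7 → 78.4 | 80.9 → 84.3 |

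The simulation error of a single entry is about √(0.8 × 0.2/1500) = 1 point. At 0 to 10% drift the change is about −3 to +0.5 points; at 30% it is a gain of 3 to 5 points.

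**The case against.** The strongest reply is that the protocol says only that sex and BMI will be controlled for. It specifies no interaction with product, no raw BMI and no software. The power collapse needs BMI to be uncentred, crossed with product and tested at zero, all together. Main effects alone, or centred BMI, do no harm. Such coding, and a period term, are often settled in a statistical analysis plan, and only the protocol was available here. This stands: a reader might infer that the primary test is bound to fail, and the text does not support that.

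A reader might also infer that the visit's fasting baseline is ignored. It is not. The incremental area is measured from that visit's own baseline, so only a further covariate is absent. Under assumed reading-error SDs of 0.1 to 0.3 mmol/l and day-to-day fasting SDs of 0.15 to 0.3 mmol/l, adding one multiplied the contrast variance by 0.77 to 1.01, a range that includes no benefit.

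Nor does omitting period bias the comparison. Order is randomised, so chance imbalance adds variance and no systematic error.

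Finally, sex and BMI are not useless everywhere. In the logistic models for symptoms, person-level covariates can change the conditional product estimate. If some data sets are dropped under the missing-data rule, a mixed model uses some between-person information. These are reasons of precision or effect modification; they do not rescue the confounding rationale, which the protocol states for all models.

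**Conclusion.** The point holds as a correction to the stated model. Confounding by sex or BMI is not possible in the complete within-person comparison that the protocol describes, and on complete data the main-effect adjustment changes nothing. The wording also admits an implementation that cuts omnibus power from about 84% to about 6% at n = 30. That size is conditional on raw BMI being crossed with product, and on an assumed alpha, an SD back-solved from the plan's own power claim, an assumed BMI distribution and an equal 25% effect at each dose. Omitting period is a smaller matter of precision, noticeable only if drift across visits is large. This is a cheap improvement to the primary analysis; it does not show that the trial's comparison is invalid.

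**What to change.** Make the change before unblinding. Trial Status reports recruitment finished and most participants through all four visits, so the time left is short.

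- Delete the confounding rationale for sex and BMI.
- Analyse glucose iAUC and insulin iAUC with product and period as fixed effects and participant as a random effect.
- If sex or BMI is kept, enter it centred, state which BMI measurement is used, and label the term as precision or as exploratory effect modification (product by sex, product by centred BMI).
- Treat a visit-baseline covariate as optional.

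No new data are needed. Period takes three degrees of freedom: with 40 complete participants, the within-person error falls from 40 × 3 − 3 = 117 to 114. If drift is small, the power change is about −3 to +0.5 points.

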## Abstract

**Background:** Worldwide sugar consumption has tripled during the last fifty years. High sugar intake is associated with weight gain, increased incidence of diabetes and has been linked with increased cardiovascular mortality. Reducing the health impact of dietary sugar and poor quality carbohydrate intake is a public health priority. IminoNorm®, a proprietary mulberry leaf extract (ME) may reduce blood glucose responses following dietary sugar and carbohydrate intake by reducing absorption of glucose from the gut. Previous research has shown that ME can reduce blood glucose and improve insulin responses in healthy subjects and also in subjects with raised fasting blood glucose levels. Mulberry leaf has an excellent safety profile. This pilot study will test a novel safe water soluble product in normoglycaemic adults in the UK to determine if it can reduce glucose absorption without increasing plasma insulin concentration.

**Methods/Design:** The trial will be a double blind, individually randomised, four-arm single dose crossover design to test the effect of three doses of ME in order to determine efficacy, dose response relationship and gastrointestinal side effects with respect to placebo. A total of 40 subjects will participate in this study and attend for four visits receiving each of the four interventions in random order.

**Discussion:** We aim to test the evidence that mulberry leaf extract can reduce blood glucose without a disproportionate increase in blood insulin responses in healthy individuals in a high-quality research study based in the UK. It is hoped that this will lead to further randomised controlled trials and an effective dietary supplement to lower blood glucose concentrations.

**Trial Registration:** ISRCTN: ISRCTN 14597438 (21/04/2015)

**Keywords:** Mulberry, Glycaemic Response, Insulinaemic Response

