## **Discussion**

In this paper, we have suggested the clinical trial design of a dietary supplement to reduce glucose excursions without a disproportionate increase in insulin release. This pilot study will influence further work on a larger scale RCT. In this study we aim to confirm the standard dose of IminoNorm that can be consumed with food. In addition, we aim to determine the magnitude of clinical effect and to measure the frequency and intensity of any gastrointestinal side effects. Based on the results, we will aim to design a larger RCT to investigate the protective effect of ME on the development of pre-diabetes and diabetes in at risk individuals or the population as a whole. The treatment effect size may be used to determine the sample size of a larger study based on similar studies on the prevention of T2DM As mentioned previously, ME may also have a positive effect on lipid profiles and we may decide to include further endpoints in future larger trials. Glucose-lowering agents show ethnic variations and future work should include assessment in more ethnically diverse populations.

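### The GI tolerability analysis names logistic regression without any term for participant, although each person contributes four visits; an ordinary fit would make the product comparison conservative

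*Protocol*

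**What the plan says.** The design is a complete crossover. The Abstract states "A total of 40 subjects will participate in this study and attend for four visits receiving each of the four interventions in random order", and Study Design adds "Participants will act as their own controls, i.e. each participant will test all four products". Under Outcomes, gastrointestinal tolerability is a secondary outcome, and the data come from every visit: "Gastrointestinal symptoms will be measured via questionnaire for 24 hours following each study visit".

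Statistical Analysis fixes a method for each type of outcome. For iAUC, the four products are to be calculated and the plan is to "compare using repeated measures ANOVA to determine whether there is a statistically significant difference in plasma glucose levels". For tolerability it says "The presence/absence of gastrointestinal symptoms in the 24 hours following the study visit will be assessed using logistic regression models". It also says "All models will control for the possible confounding effects of sex and BMI". No participant effect, clustering, correlation structure or period term is mentioned for the logistic model. The section does not say that visits will be treated as independent.

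The Discussion gives a further aim, "to measure the frequency and intensity of any gastrointestinal side effects", and Outcomes provides 10-cm line scales for it.

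**The concern.** The section recognises the repeated-measures structure for the continuous outcome and is silent on it for the binary one. An analyst who follows the text would most naturally fit an ordinary logistic regression of symptom status on product, sex and BMI across all visit records. That model assumes the records are independent, and four visits by the same person are unlikely to be.

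The direction of the error matters here. Positive correlation helps a within-person comparison, and an independence model throws that benefit away, so the test of product on symptoms becomes conservative. For an efficacy outcome that costs power. For a harm outcome it also tilts the result towards finding no difference in tolerability. The Objectives include tolerability at each of the three doses, and the Discussion says the results will inform the standard dose and a larger trial.

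**Working it through.** **Inputs from the protocol.** 40 participants × 4 visits = up to 160 binary records; every participant takes all four products; the covariates are sex and BMI. There is no figure to reproduce: the protocol gives no symptom rate, within-person correlation or power for this outcome. The only power statement concerns iAUC.

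**Assumptions.** Within-person correlation rho of the binary responses, and the symptom rates, are shown as ranges. Tests are two-sided at 5%.

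**Step 1: analytic size of the error.** Take two products compared within n people, each response with variance s² and correlation rho.

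- Variance of the difference under independence: 2s²/n.
- True variance: 2s²(1 − rho)/n.
- Ratio of ordinary to true standard error: 1/√(1 − rho).
- True size of a nominal 5% test: 2[1 − Φ(1.96/√(1 − rho))].

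| rho | SE ratio | True size |
|---|---|---|
| 0 | 1.00 | 5.0% |
| 0.1 | 1.05 | 3.9% |
| 0.2 | 1.12 | 2.8% |
| 0.3 | 1.20 | 1.9% |
| 0.5 | 1.41 | 0.6% |

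**Step 2: simulation under no effect.** 2,000 trials per scenario, 40 people × 4 products, participant random intercept, model with linear dose, sex and BMI, symptom rate 20% on every product.

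- rho about 0.34: ordinary SE of the dose effect 0.547, actual spread 0.475 (ratio 0.547/0.475 = 1.15); rejection rate 2.0%.
- rho about 0.51: 0.547 against 0.416 (ratio 1.31); rejection rate 0.6%.

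The simulated SE ratios are somewhat below the formula (1/√0.66 = 1.23 and 1/√0.49 = 1.43), but the direction is the same and the test sizes agree closely.

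For BMI, which varies between people, the error reverses. At rho about 0.34 the ordinary SE is 0.214 against an actual 0.326, and a nominal 5% test rejects in 17% of trials.

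**Step 3: simulation of power for the dose effect, n = 40.** Ordinary SE against SE clustered on participant:

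| Assumed rates, placebo to highest dose | rho about | Ordinary | Clustered | Gain (points) |
|---|---|---|---|---|
| 20/25/30/40% | 0 | 57% | 57% | 0 |
| | 0.14 | 55% | 62% | 7 |
| | 0.34 | 55% | 73% | 18 |
| | 0.46 | 55% | 82% | 26 |
| 20/27.5/35/50% | 0.14 | 88% | 90% | 2 |
| | 0.32 | 89% | 95% | 7 |
| | 0.41 | 92% | 99% | 6 |
| 10/12.5/15/20% | 0.11 | 24% | 29% | 6 |
| | 0.30 | 21% | 35% | 14 |

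Powers and gains are rounded separately. The clustered SE rejected in 5.0% to 6.2% of null trials, so a small part of each gain reflects its slight optimism at 40 clusters. That is why the fix asks for a small-sample correction.

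**Step 4: a single contrast.** A separate simulation of 500 mg against placebo (600 trials per scenario, ordinary logistic against GEE) points the same way. At rho about 0.46, power is 25% against 45% for rates of 31% and 46%, and 58% against 81% for 31% and 54%. At rho about 0.27, it is 48% against 63% for 25% and 46%.

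**The case against.** The strongest reply is that independence is inferred. Random-intercept, GEE and conditional models are all logistic regressions, the protocol describes the trial as a repeated-measures crossover, and a correlation structure for a secondary outcome is often left to a statistical analysis plan, which is not at hand here. This stands in part: a reader might infer that the protocol prescribes an independence analysis, and it does not say so. But the section is not simply silent. It assigns a method to each outcome and gives only one of them a within-participant form. The sex and BMI adjustment also sits badly with a conditional model, where sex would drop out. The ordinary fit remains the natural reading, and nothing in the text steers an analyst away from it.

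A reader might also infer that a real increase in symptoms would probably be missed. The documents do not support that, because they give neither rates nor correlation. In the scenarios above, a rise from 20% to 50% is detected by the ordinary model in 88% to 92% of trials when rho is 0.14 to 0.41. A rise from 10% to 20% is missed in about 65% to 71% of trials even with the clustered SE, mainly because the trial is small. With rho near 0 nothing is lost.

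Finally, the absence of a named model for the 10-cm scores is mostly an omission that an analysis plan could fill. Descriptive reporting could meet an aim worded as measurement.

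**Conclusion.** The point holds in conditional form. If the model is fitted as ordinary logistic regression, and if within-person correlation is positive, the standard errors of the product or dose effects are too large and the tolerability test is conservative. The statement that standard errors are too large applies to those terms only; for sex and BMI they are too small.

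A real dose-related increase is then more likely to be missed than it need be. That is as far as the evidence goes. The cost depends on assumed inputs: none at rho near 0, about 7 points at rho 0.14, and about 18 to 26 points at rho 0.34 to 0.46, for rates of 20/25/30/40%. It is smaller when the increase is large.

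Severity is moderate. The outcome is secondary, the trial describes itself statistically as a pilot, no decision rule is tied to this test, and the primary iAUC analysis is unaffected.

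**What to change.** In Statistical Analysis, replace the unqualified logistic regression with a logistic model that accounts for participant, with product and period as factors. Either a random intercept for participant, or GEE with exchangeable correlation and a small-sample correction, would serve. Name one in advance, since the first gives participant-specific and the second population-average odds ratios. If events are too sparse for the model, use exact paired (McNemar) tests of each dose against placebo.

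Optionally, analyse the 10-cm frequency and intensity scores within participant as well.

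The cost is a sentence or two of text and slightly more analysis work. No new data are needed, as the questionnaire is already scheduled at every visit. Trial Status reports that recruitment has finished and most participants have completed all visits, so the change should be dated and recorded before the randomisation code is broken for analysis.
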